## 1. PROJECT INFORMATION

### 1.1. Project Title:

Effectiveness of a New Neural Motor Recruitment Method (NEUROM) Combined with Transcranial Direct Current Stimulation (tDCS) to Induce and Guide Motor Recovery in Paraplegic Patients.

### 1.3. Study Setting:

- Rahma Hospital for Rehabilitation (Tripoli, North Lebanon)
- Physical Therapy Center, Faculty of Public Health (Hadath, Beirut)

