## 3. METHODOLOGY

### 3.1. Study Design:

Single-blind, randomized controlled clinical trial.

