### 3.3. Randomization:

Participants will be randomly assigned into three groups using a web-based random number generator ([www.random.org](http://www.random.org)) in a 1:2:2 ratio:

1. **Reference Group ( $n = 10$ ):** Conventional physical therapy.
2. **NEUROM Group ( $n = 20$ ):** Neural Motor Recruitment protocol.
3. **NEUROM + tDCS Group ( $n = 20$ ):** NEUROM protocol + tDCS.

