## 7. ETHICAL CONSIDERATIONS

- **Informed Consent:** Written informed consent will be obtained from all participants in Arabic (their native language). The consent form explains the study purpose, procedures, risks, and the right to withdraw at any time. (See attached *Consent Form*).
- **Safety Monitoring:** A senior research specialist will monitor all sessions. Any adverse events (e.g., skin redness, dizziness) will be recorded and reported immediately. If a patient reports severe symptoms (score 5/10 on the safety questionnaire), they will be withdrawn from the study.
- **Risk/Benefit Analysis:** The risks of tDCS (mild skin irritation, headache) are minimal and transient. The potential benefits (motor recovery) are significant for this patient population.

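### Section 3.3 does not tie the 10/20/20 allocation to the two sites, so a chance site imbalance against the 10-patient reference group is plausible and cheaply avoided

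*Protocol*

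**What the plan says.** Protocol section 1.3 (Study Setting) lists a rehabilitation hospital, "Rahma Hospital for Rehabilitation (Tripoli, North Lebanon", and a university centre, "Physical Therapy Center, Faculty of Public Health (Hadath, Beirut". It gives no recruitment split between them.

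Section 3.3 (Randomization) states the method: "Participants will be randomly assigned into three groups using a web-based random number generator", in a 1:2:2 ratio. The arm sizes are given for the whole trial: "Reference Group ( $n = 10$ ): Conventional physical therapy", "NEUROM Group ( $n = 20$ ): Neural Motor Recruitment protocol" and "NEUROM + tDCS Group ( $n = 20$ ): NEUROM protocol + tDCS". No site, stratum or block is named there or elsewhere in the protocol.

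Two other statements bear on the point. Section 3.1 calls the study a "Single-blind, randomized controlled clinical trial", without saying who is blinded. Section 7 says "A senior research specialist will monitor all sessions", which is a monitoring role and not an examining one. The protocol does not describe who treats or examines at each site, or whether all three arms are delivered at both.

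**The concern.** The section that sets the allocation method leaves out the two-site structure set up in section 1.3. The reference group has 10 patients and serves both comparisons implied by the hypothesis in section 2: NEUROM against conventional therapy, and NEUROM with tDCS against conventional therapy. In a group that small, moving two patients from one site to the other changes the site share by 20 percentage points.

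If outcomes differ by site, through patient mix, delivery or grading of the 0 to 5 muscle scores, an imbalance in site shifts an unadjusted contrast. A small site could also end with one reference patient or none, leaving little or no comparison within that site. Stratified allocation has to be in place before the first patient is randomized, so a later statistical analysis plan cannot supply it.

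**Working it through.** **Inputs from the protocol.** N = 50 (section 3.2); ratio 1:2:2 and arm sizes 10, 20, 20 (section 3.3); two sites (section 1.3).

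**Assumption.** Patients per site are not stated. The smaller site is taken to hold s = 10, 15, 20 or 25 of the 50.

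**Step 1, the plan's own figure.** 50 × 1/5 = 10 and 50 × 2/5 = 20, so 10/20/20 is reproduced exactly.

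**Step 2, spread of the imbalance.** Let D be the smaller site's share of the reference group minus its share of one NEUROM arm. Under random allocation with fixed totals and no stratification, E(D) = 0 and, with p = s/50,

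SD(D) = √[ (50/49) · p(1 − p) · (1/10 + 1/20) ].

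For s = 25: √(1.0204 × 0.25 × 0.15) = 0.196.

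**Step 3, exact probabilities.** With a, b and c patients of the smaller site in the three arms (a + b + c = s), the probability is C(10,a) · C(20,b) · C(20,c) / C(50,s). Summing over the relevant cells gives:

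| Quantity | s = 10 | s = 15 | s = 20 | s = 25 |
|---|---|---|---|---|
| SD(D) | 0.156 | 0.179 | 0.192 | 0.196 |
| P(absolute D ≥ 0.20), reference vs one NEUROM arm | 27% | 33% | 36% | 37% |
| P(absolute D ≥ 0.30), reference vs one NEUROM arm | 8% | 12% | 15% | 16% |
| P(difference ≥ 0.20), reference vs other 40 pooled | 18% | 25% | 28% | 29% |
| P(difference ≥ 0.30), reference vs other 40 pooled | 2% | 5% | 7% | 7% |
| P(at most one reference patient at smaller site) | 35% | 12% | 3% | 0.5% |
| P(no reference patient at smaller site) | 8.3% | 1.8% | 0.3% | 0.03% |

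**Step 4, effect on an unadjusted contrast.** Shift = imbalance × site effect. For an assumed site effect of 0.5 SD, the shift is 0.20 × 0.5 = 0.10 SD or 0.30 × 0.5 = 0.15 SD. For 0.25 SD it is 0.05 or 0.075 SD, and for 1.0 SD it is 0.20 or 0.30 SD. For scale, the standard error of a 10 versus 20 contrast is √(1/10 + 1/20) = 0.387 SD, so 0.10 SD is about a quarter of it (0.10/0.387 = 0.26).

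**Step 5, what adjustment achieves.** If the site effect is additive, a site term removes the shift. The cost in precision follows from the within-site information, the sum over sites of n(ref) · n(NEUROM) / [n(ref) + n(NEUROM)]. With balanced sites this is 10 × 20/30 = 6.667.

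- Imbalance of 0.30 (7 of 10 against 8 of 20): 7 × 8/15 + 3 × 12/15 = 3.733 + 2.400 = 6.133. Standard error ratio √(6.667/6.133) = 1.04.
- No reference patient at the smaller site (0 of 10 against 5 of 20): 0 + 10 × 15/25 = 6. Ratio √(6.667/6) = 1.05, with the whole contrast estimated at the other site.

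**Step 6, after the change.** With a separate 1:2:2 list per site and complete blocks, the reference group holds one fifth of each site's patients: 2, 3, 4 or 5 at a smaller site of 10, 15, 20 or 25. The site shares are then equal across arms, apart from an incomplete last block.

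**The case against.** The strongest reply is that randomization already deals with this. The expected site imbalance is zero, and chance imbalance in one covariate is part of ordinary sampling error. That stands. A reader might infer that arm is confounded with site. That would need an arm, or the stimulation device, to be tied to one site, which the protocol neither states nor excludes.

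A second reply is that adjustment is enough. This stands for the main contrast: under an additive site effect, a site term removes the shift for a 4% to 5% larger standard error in the cases worked above. It would therefore be wrong to say that later analysis cannot repair an imbalance. What it cannot do is create reference patients at a site that received hardly any. The protocol does not promise within-site comparisons, so this loss is limited. Choosing analysis factors is normally left to the statistical analysis plan, and their absence from the protocol is not at issue here.

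Third, differences between the sites are only inferred. The two names suggest unlike settings, but no section gives staffing, examiners or patient mix by site. Section 4.1 describes a standardized conventional programme, and sections 4.2 and 4.3 set out delivery of the other arms, which narrows the room for differences. If one examiner grades a patient at both baseline and week 3, a stable difference in strictness would largely cancel in change scores.

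Fourth, the figures depend on the split. The 35% needs a 40/10 split, and with equal sites it is 0.5%. Against both NEUROM arms pooled, imbalances are rarer.

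Finally, section 3.3 does not say that site lists are ruled out. It does state a method and trial-wide totals, however, and as written that method leaves site to chance.

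**Conclusion.** The point holds as a cheap improvement to the allocation method, not as an error that undermines the trial. Sections 1.3 and 3.3 together leave the balance of sites across arms to chance, and the 10-patient reference group makes a noticeable imbalance plausible: a 27% to 37% chance of 20 points or more against a given NEUROM arm. The risk of at most one reference patient at a site is serious only if that site is small.

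The probabilities rest on an assumed smaller site of 10 to 25 patients and on fixed 10/20/20 totals. The size of any shift rests on an assumed site effect, for which the protocol gives no figure. If outcomes do not differ by site, nothing is biased. If they do, the result is avoidable error in both comparisons with the reference group, most of which a site term would recover. The documents do not support reading this as systematic bias or as damage beyond repair.

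**What to change.** In section 3.3, replace the single allocation with two separately generated lists, one per site. Each list uses shuffled blocks that keep the 1:2:2 ratio, in mixed sizes such as 5 and 10, with block sizes and upcoming assignments concealed from the staff who enrol patients. State that site is a factor in the between-arm comparisons.

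The cost is a sentence or two in the protocol and a second list, and no treatment changes. There are three downsides. An incomplete last block at each site can move the totals by a patient or two from 10/20/20. One degree of freedom is spent on site. Blocks also carry some predictability: in a block of 5, once the single reference assignment has been used, every remaining place goes to one of the two NEUROM arms. Mixed, concealed block sizes reduce this but do not remove it.

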### 1.4. Proposed Duration:

2 years (Anticipated Start Date: December 2022)

### 1.5. Objectives:

In this study, we propose a new experimental rehabilitative protocol for Traumatic Spinal Cord Injury (TSCI) patients called the **Neural Motor Recruitment Method (NEUROM)**. This method is based on histological and functional reorganization models following TSCI, Motor Imagery (MI) concepts, and targeted sensory inputs related to motor recovery. We hypothesize that this new method can enhance sparing-induced plasticity and increase motor and sensory recovery in SCI patients, especially when

combined with Transcranial Direct Current Stimulation (tDCS).

## 2. SUMMARY AND RATIONALE

### Background:

Traumatic Spinal Cord Injury (TSCI) is a catastrophic event resulting in motor paralysis and sensory loss. While spontaneous recovery is possible in the acute phase, chronic paraplegia is traditionally viewed as a stable condition with limited potential for further recovery. Recent evidence suggests that the adult spinal cord retains significant plasticity even in the chronic phase. We propose a "bottom-up" approach using a specific motor recruitment protocol (NEUROM) combined with a "top-down" cortical prime using tDCS to enhance this plasticity.

### Hypothesis:

We hypothesize that the NEUROM method, especially when combined with anodal tDCS, will induce greater sensorimotor recovery than conventional therapy alone in patients with chronic paraplegia.

## 3. METHODOLOGY

### 3.1. Study Design:

Single-blind, randomized controlled clinical trial.

### 3.2. Participants:

- **Target Sample Size:**  $N = 50$
- **Inclusion Criteria:**
  1. Age between 16 and 45 years.
  2. Diagnosis of traumatic spinal cord injury (TSCI).
  3. Chronic phase (3 months post-injury).
  4. Level of injury: Lower dorsal (T1–T10) or Thoracolumbar (T11–L1).
  5. ASIA Impairment Scale (AIS) grade A, B, or C.
- **Exclusion Criteria:**
  1. Traumatic Brain Injury (TBI) or neuropsychiatric comorbidities.
  2. Severe spasticity (Modified Ashworth Scale).
  3. Contraindications to tDCS (metal in head, pacemaker, history of seizures).
  4. Use of sodium channel blockers (e.g., carbamazepine).

### 3.3. Randomization:

Participants will be randomly assigned into three groups using a web-based random number generator ([www.random.org](http://www.random.org)) in a 1:2:2 ratio:

1. **Reference Group ( $n = 10$ ):** Conventional physical therapy.
2. **NEUROM Group ( $n = 20$ ):** Neural Motor Recruitment protocol.
3. **NEUROM + tDCS Group ( $n = 20$ ):** NEUROM protocol + tDCS.

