## 5. OUTCOME MEASURES

**Time Points:** Baseline (Pre) and Week 3 (Post-Intervention).

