### 1. ASIA Impairment Scale (ISNCSCI):

- **Motor Score (LEMS):** 5 key muscles per leg (0-5 scale). Max = 50.
- **Sensory Score:** Light Touch and Pin Prick at 12 key points per leg. Max = 48 each.

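### Stratifying the 1:2:2 allocation by AIS A/B versus C would cheaply protect precision, because both comparisons with conventional therapy rest on 10 reference patients

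*Protocol*

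**What the plan says.** Protocol section 3.3 is the whole description of allocation. Participants are "randomly assigned into three groups using a web-based random number generator", in a 1:2:2 ratio, giving 10 patients on conventional therapy, 20 on NEUROM and 20 on NEUROM plus tDCS. Neither that section nor any other names a stratification factor, blocking or minimisation.

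Section 3.2 admits "ASIA Impairment Scale (AIS) grade A, B, or C" with no cap or quota by grade. Section 5 lists the lower-extremity motor score (LEMS), built from "5 key muscles per leg (0-5 scale). Max = 50", among the outcomes and measures it at baseline and at week 3. The hypothesis in section 2 is greater sensorimotor recovery than with conventional therapy alone, so each NEUROM arm is to be compared with the reference arm.

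**The concern.** By definition of the scale, AIS A and B are motor-complete and C is motor-incomplete. The grade therefore bears on baseline LEMS and plausibly on how far LEMS can move in three weeks. The protocol does not say how much it matters.

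In an arm of 10, one patient moves the case mix by 10 percentage points. Because that arm serves both comparisons, an unusual mix in it shifts both contrasts together. What is at stake is precision and how readily the single realised result can be read, not the validity of the test.

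**Working it through.** **Inputs from the protocol.** N = 50 (3.2); ratio 1:2:2 and arms of 10/20/20 (3.3); AIS A, B and C without quota (3.2); LEMS from 0 to 50 (5).

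**Inputs assumed, because the protocol does not give them.** Overall AIS C share: 10% to 50%. Difference *g* in mean LEMS gain between C and A/B patients: 2 to 4 points.

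**Step 1: the plan's own figure.** 50 × 1/5 = 10 and 50 × 2/5 = 20, so 10/20/20 reproduces.

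**Step 2: chance imbalance with fixed arm sizes and no stratification.** Let K of the 50 patients be AIS C, with a, b and c of them falling in the reference, NEUROM and NEUROM plus tDCS arms. Then

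P(a, b, c) = C(10,a) × C(20,b) × C(20,c) / C(50,K), with a + b + c = K.

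The gap between the reference and NEUROM arms is |a/10 − b/20|. It is at least 20 points when |2a − b| ≥ 4 and at least 30 points when |2a − b| ≥ 6. Summing the exact probabilities, with gaps counted in either direction:

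| AIS C share (K) | ≥20 points, one given NEUROM arm | ≥20 points, at least one NEUROM arm | ≥30 points, one given arm | ≥30 points, at least one arm | 0-1 AIS C in reference arm |
|---|---|---|---|---|---|
| 10% (5) | 13% | 20% | 1% | 3% | 74% |
| 20% (10) | 27% | 39% | 8% | 14% | 35% |
| 30% (15) | 33% | 47% | 12% | 21% | 12% |
| 40% (20) | 36% | 51% | 15% | 25% | 3% |
| 50% (25) | 37% | 53% | 16% | 26% | 0.5% |

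**Step 3: typical size of the gap.** SD = √[p(1 − p) × (50/49) × (1/10 + 1/20)]. At p = 0.3 this is √(0.21 × 1.0204 × 0.15) = 0.179, or about 18 points.

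**Step 4: effect on an unadjusted LEMS contrast.** Shift = gap × *g*. A 20-point gap gives 0.2 × 2 = 0.4 to 0.2 × 4 = 0.8 points. A one-SD gap at 30% AIS C gives 0.179 × 2 = 0.36 to 0.179 × 4 = 0.72 points.

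**Step 5: the same check with stratified blocks.** A complete block of 5 (1:2:2) within a stratum gives every arm the same share of that stratum, so only incomplete final blocks can create a gap. In simulation with blocks of 5 within A/B and within C, no gap of 20 points or more occurred for any AIS C count tested from 8 to 25. The largest gap was 10 points.

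**Note on the fixed sizes.** If the generator drew each patient independently at 1:2:2, the reference arm would be exactly 10 with probability C(50,10) × 0.2¹⁰ × 0.8⁴⁰ = 14%, and would be 7 or fewer or 13 or more with probability 38%. The stated 10/20/20 implies some restriction that section 3.3 does not describe. Steps 2 to 4 take the stated sizes as fixed.

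**The case against.** The strongest reply is that nothing in section 3.3 is wrong. Unstratified randomisation is unbiased on average and keeps the type I error, and chance imbalance is part of the sampling error that a valid interval already covers. That stands. A reader might infer that the allocation is invalid, or that imbalance would probably produce or hide a treatment effect. The documents support neither. They give no AIS C share, no difference in gain by grade and no SD of LEMS change, so the shifts in Step 4 cannot be set against a standard error. LEMS is also not named as primary; sensory scores and the movement-attempt interview stand beside it.

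The size is easily overstated too. The 47% at a 30% share is the chance of a gap against at least one of two arms, in either direction. For one given comparison it is 33%, about half of that in a given direction, and at a 10% share it is 13%.

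The analysis plan, which is not shown, may adjust for AIS grade and baseline score. At shares of 30% and above that would usually work, because 0-1 AIS C patients in the reference arm occurs in at most 12% of allocations. It is weaker at 20%, where the figure is 35%. At 10% stratification itself helps little: 5 × 1/5 = 1, so about one AIS C patient is all the reference arm would get.

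Finally, a reader might take the short randomisation text as evidence of poor allocation concealment. That is a separate matter, and this point does not rest on it.

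**Conclusion.** The point holds as an inexpensive gain in precision and robustness, not as an error in the plan. For AIS C shares of 20-50%, a given NEUROM arm has a 27-37% chance of differing from the reference arm by 20 points or more in AIS C share; at 10% it is 13%. These probabilities depend only on the stated arm sizes and the assumed share. The consequence, 0.4-0.8 LEMS points for a 20-point gap, depends also on the assumed 2-4 point difference in gain and on an unadjusted comparison. Confidence is high in the probabilities and moderate at best in how much they matter.

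**What to change.** In section 3.3, specify permuted blocks in the 1:2:2 ratio, stratified by AIS A/B versus C. Add no further strata, such as injury level or centre, since 50 patients in three arms will not support them. Include the AIS stratum and the baseline score in the comparison of arms, here or in the analysis plan.

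The cost is a paragraph and a new allocation sequence before the first patient. AIS grade is already needed for eligibility, so no new data are collected. The change is not free: if final blocks are incomplete, arm totals can miss 10/20/20. With blocks of 5 and an AIS C count that is not a multiple of 5, complete blocks cover 45 patients (9/18/18). The last 5 come from two partial blocks holding 0-2 reference patients and 0-4 from each NEUROM arm, so the reference arm ends at 9-11 and each NEUROM arm at 18-22. Larger blocks could widen this.

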## 4. GENERAL EXPERIMENTAL PROCEDURE

### 4.1. Conventional Rehabilitation Program (Reference Group)

Patients will receive a standardized conventional program including:

- Passive and active mobilization.
- Strengthening and endurance exercises.
- Neuromuscular facilitation techniques.
- **Dosage:** 5 sessions/week for 3 weeks.

### 4.2. Neural Motor Recruitment (NEUROM) Method

This closed-loop protocol consists of two phases:

- **Phase 1 (Week 1):** Daily Motor Imagery (MI) training combined with 20 minutes of static stretching (hamstrings/soleus).
- **Phase 2 (Weeks 2-3):** Active NEUROM sessions.
  - **Visual:** Patients view a 5-minute video of feet performing dorsi- and plantarflexion on a large screen (43-inch, 3.5m distance).
  - **Cognitive:** Audio instructions guide the patient to perform Kinesthetic Motor Imagery ("Imagine yourself performing the movement...").
  - **Sensory:** Concurrent peripheral sensory stimulation.

### 4.3. Transcranial Direct Current Stimulation (tDCS)

- **Device:** Starstim NE wireless neurostimulator (Neuroelectronics®, Barcelona).
- **Montage:** Bi-hemispheric (C3/C4). Alternating anode/cathode placement on Left/Right M1 daily.
- **Parameters:** 1 mA intensity, 20 minutes duration, 7-second ramp.
- **Safety:** A neurologist will screen patients for contraindications. A specific questionnaire for adverse effects (headache, skin irritation) will be administered before and after each session.

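### The adverse-effect questionnaire is scheduled only in the tDCS procedure; if it is used only there, adverse events by arm will not be comparable

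*Protocol*

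**What the plan says.** Section 3.3 of the Protocol allocates 50 patients 1:2:2: 10 to the Reference group ("Conventional physical therapy"), 20 to NEUROM ("Neural Motor Recruitment protocol") and 20 to the combined group ("NEUROM protocol + tDCS").

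Section 4.3 applies only to the combined group. Its safety item, beside the neurologist's screening for contraindications, states: "A specific questionnaire for adverse effects (headache, skin irritation) will be administered before and after each session". Sections 4.1 and 4.2, which set out the procedures for the other two groups, contain no counterpart.

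Section 7 has three provisions not tied to an arm:

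- On withdrawal, with no group named: "If a patient reports severe symptoms (score 5/10 on the safety questionnaire), they will be withdrawn from the study".
- On observation, again without limiting it to one group: "A senior research specialist will monitor all sessions".
- On documentation, with no method of elicitation given: "Any adverse events (e.g., skin redness, dizziness) will be recorded and reported immediately".

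The same section concludes: "The risks of tDCS (mild skin irritation, headache) are minimal and transient". Section 5 lists ISNCSCI and AMA as outcomes. It names no safety outcome and no between-arm safety comparison.

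**The concern.** Headache and dizziness are subjective. An observer learns of them if the patient volunteers them or is asked, and asking finds more. If one arm is questioned twice per session and the others are not, the recorded frequencies differ through the collection method even when the true risks are equal.

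The contrast that matters most is NEUROM + tDCS against NEUROM, because it is the only one that isolates the added stimulation. Headache could also come from watching a screen, sustained imagery or effort, so the NEUROM group is needed as a background rate. NEUROM is itself experimental, and its own harms would be under-recorded. Who is asked, and when, is a data-collection procedure: no later analysis can recover symptoms that nobody asked about.

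**Working it through.** **1. Which arms complete the questionnaire?** The text on each group, side by side:

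| Group | n | Questionnaire scheduled in its procedure | Section 7 provisions |
|---|---|---|---|
| Reference (4.1) | 10 | none | monitoring, recording |
| NEUROM (4.2) | 20 | none | monitoring, recording |
| NEUROM + tDCS (4.2 and 4.3) | 20 | pre- and post-session (4.3) | monitoring, recording |

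The natural reading is that the sessions in section 4.3 are tDCS sessions, which gives 20 patients questioned and 10 + 20 = 30 not. Against that, the withdrawal rule in section 7 presupposes a questionnaire score for any patient. If, as seems likely, it means the section 4.3 form, the two sections do not agree clearly on who has a score.

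**2. Size of the distortion if only the tDCS group is questioned.** The protocol gives no adverse-event rate, so there is no stated figure to reproduce and the inputs below are assumptions. Let p be the true proportion of patients with a symptom, equal in all arms (tDCS adds nothing). Let questioning capture every affected patient, and let c be the fraction captured without it.

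- Apparent risk ratio = p / (p × c) = 1/c
- Apparent risk difference = p(1 − c)

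| c | Risk ratio | Risk difference, p = 0.1 | p = 0.2 | p = 0.4 | p = 0.6 |
|---|---|---|---|---|---|
| 0.75 | 1.33 | 0.025 | 0.05 | 0.10 | 0.15 |
| 0.50 | 2.0 | 0.05 | 0.10 | 0.20 | 0.30 |
| 0.25 | 4.0 | 0.075 | 0.15 | 0.30 | 0.45 |
| 1.00 (all arms questioned) | 1.0 | 0 | 0 | 0 | 0 |

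In counts, p = 0.2 and c = 0.5 give an expected 4 of 20 against 2 of 20. At p = 0.4 and c = 0.25 it is 8 of 20 against 2 of 20.

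**3. Chance of a spurious two-sided Fisher p < 0.05, 20 against 20**, by exact binomial enumeration: 7.2% at p = 0.2, c = 0.5; 19.2% at p = 0.4, c = 0.5; 49.2% at p = 0.4, c = 0.25. With equal questioning (c = 1) it is 1.2% to 2.4% for p from 0.1 to 0.6.

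**4. Sensitivity to the model.** Suppose instead that capture acts on each event. With background rate q per session, n independent sessions and P(at least one recorded) = 1 − (1 − q × c)^n, take n = 15 (assumed, because the number of tDCS sessions is not stated; 5 per week for 3 weeks is the Reference schedule):

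- q = 0.02: questioned 1 − 0.98^15 = 26.1%. Unquestioned at c = 0.75, 0.5 and 0.25: 1 − 0.985^15 = 20.3%, 1 − 0.99^15 = 14.0%, 1 − 0.995^15 = 7.2%. Ratios about 1.3, 1.9 and 3.6.
- q = 0.05: questioned 1 − 0.95^15 = 53.7%. Unquestioned: 1 − 0.9625^15 = 43.6%, 1 − 0.975^15 = 31.6%, 1 − 0.9875^15 = 17.2%. Ratios about 1.2, 1.7 and 3.1.

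The range is much the same. The result is driven by c, about which the protocol is silent.

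**The case against.** The strongest reply is that the protocol makes no between-arm safety comparison. Its hypothesis and outcomes concern sensorimotor recovery, the questionnaire protects participants during a device procedure, and the statement on tDCS risk justifies the trial ethically without being a hypothesis. That is correct: a reader who infers that a planned safety comparison is biased goes beyond the document. What remains is that any listing of adverse events by arm would carry the distortion.

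Three further limits stand.

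- That the other 30 patients are never asked is an inference from where the sentence sits. Section 7 words the withdrawal rule for any patient, so the text is ambiguous.
- Adverse events in the other groups are not left to chance, since every session is monitored. Monitoring is weaker than questioning for subjective symptoms, but it is systematic.
- A reader might infer that symptoms cannot be attributed to tDCS at all. Pre- and post-session administration does show within-session change, and skin irritation is less plausibly caused by imagery or a video. But tDCS is combined with NEUROM, so the change includes any effect of the NEUROM session unless the NEUROM group is asked in the same way.

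A fourfold inflation might also be quoted as the expected size. It is only the extreme of the assumed range.

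Finally, no sham is described, so patients may know whether they are stimulated. Equal questioning would not remove expectation-driven reporting. That limits what the fix achieves, but it is no reason to keep unequal questioning.

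**Conclusion.** The point holds conditionally. The document schedules active questioning only with tDCS and gives no elicitation method elsewhere. If it is followed that way, adverse-event frequencies by arm are not comparable, and the bias runs against tDCS and in favour of NEUROM and Reference. The direction is predictable, but the size is not determinable from the protocol. Under equal true risk, full capture with questioning and 25% to 75% capture without it, the spurious patient-level risk ratio is about 1.3 to 4.

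Unequal questioning does not in itself alter the ISNCSCI or AMA results. There is one related consequence: if only the tDCS group has a questionnaire score, the withdrawal rule can be triggered only there, and differential withdrawal could then reach the week 3 comparison. The defect should be corrected because it is cheap to remove now and cannot be repaired after data collection.

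**What to change.** Move the questionnaire sentence from section 4.3 to section 7 and state that the same form is given at the start and end of every session, on the same schedule, in all three groups. Report solicited events by arm on that common basis, separately from events noted through monitoring, and acknowledge that without a sham some expectation-driven reporting will remain.

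Reconcile sections 4.3 and 7 on which arms the questionnaire-based withdrawal rule covers. Extending the form could bring 30 more patients within that rule, so the scope must be stated deliberately. No view is taken here on the rule or its threshold.

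The cost is a short amendment and a few minutes per session for 30 patients. A specialist already monitors all sessions, so no additional staff should be needed.
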